## Abstract

**Background:**

Radical hysterectomy (RH) is considered a cornerstone in the treatment of early-stage cervical cancer. However, the debate surrounding the optimal surgical approach, whether minimally invasive or open surgery, remains controversial. The objective of this trial is to evaluate the survival outcomes of cervical cancer patients who undergo different surgical approaches.

**Methods:**

This study is designed as a prospective, multicenter, open, parallel, and randomized controlled trial. A total of 500 patients diagnosed with stage IA1 with LVSI, IA2, IB1, or IB2 (2018 FIGO) will be recruited. Recruitment of participants started in November 2020. The participants will be randomly assigned to one of three groups: conventional laparoscopic RH, gasless laparoscopic RH, or abdominal RH. The primary endpoint of this trial is the 2-year disease-free survival (DFS) rate. The secondary endpoints will include the 2-year overall survival (OS) rate, 5-year DFS/OS, recurrence rates, operation time, intraoperative blood loss, surgery-related complications, and impact on quality of life (QoL).

**Discussion:**

We expect this trial to provide compelling and high-quality evidence to guide the selection of the most appropriate surgical approach for early-stage cervical cancer.

**Clinical trial registration:**

Chinese Clinical Trial Register, identifier ChiCTR2000035515.

## Introduction

1

Cervical cancer ranks as the fourth most common cancer in women, with approximately 604,127 new cases in 2020 worldwide (1). Radical hysterectomy (RH) with pelvic lymphadenectomy is widely regarded as the standard treatment for early-stage cervical cancer. Since the introduction of laparoscopic radical hysterectomy (LRH) in the 1990s (2), minimally invasive surgery (MIS), whether performed via laparoscopy or robotic surgery, has gained widespread acceptance as an alternative to abdominal radical hysterectomy (ARH) due to its various benefits, including reduced morbidity, shorter hospital stays, and quicker recovery times (3–6). A number of retrospective studies have reported the feasibility, advantages, and oncologic safety of the MIS approach (7–9). Moreover, the application of ultra-minimally invasive surgery for gynecological procedures was further explored, and showed good feasibility and safety (10). However, the famous Laparoscopic Approach to Carcinoma of the Cervix (LACC) trial in 2018, a multicenter, randomized, controlled trial (RCT), demonstrated that MIS was associated with lower rates of disease-free survival and overall survival compared to open surgery in women with early-stage cervical cancer (11). A similar finding was obtained in a retrospective analysis using the National Cancer and Surveillance, Epidemiology, and End Results (SEER) data (12). Consequently, guidelines such as those provided by the National Comprehensive Cancer Network (NCCN) and the European Society of Gynecological Oncology (ESGO) have recommended the open abdominal approach as the “standard and recommended approach to radical hysterectomy” (13, 14).

However, it should be acknowledged that the LACC trial also has some weaknesses (15). For instance, the survival rate of the open surgery group in the LACC trial was too high, much higher than that reported previously. Patients with recurrence were concentrated in 14 out of 33 centers, implying the presence of quality deviations among different centers in the trial. In contrast, reports from some recently published retrospective studies and meta-analyses have suggested that MIS is not inferior to open surgery for treating early-stage cervical cancer (16–19). Notably, in the subgroup analysis of the LACC trial, no survival difference was found between MIS and open surgery for patients with stage IB1 (<2 cm) (20). This finding has been corroborated by several other retrospective studies (21). Consequently, the need for additional high-quality RCTs is evident.

Certain hypotheses have been proposed to explain the poorer prognosis associated with MIS, including the use of a uterine manipulator, intracorporeal colpotomy, and the potential spillage of cells during pelvic lymphadenectomy (15). Notably, an observational study of 693 patients found that MIS with protective vaginal closure resulted in oncologic outcomes similar to those of open surgery (hazard ratio (HR): 0.63, 95% confidence interval (CI): 0.15–2.59) (21). In the Atsushi et al. study, they observed that the 3-year DFS rates (NLNT 92.4%; ARH 94.0%) and overall survival rates did not differ significantly between the MIS and open surgery groups by using the no-look no-touch (NLNT) technique, which included creation of the vaginal cuff, bagging the specimen and proceeding without an intra-uterine manipulator (22). Nevertheless, the debate regarding whether oncologic outcomes of MIS, with modifications to prevent tumor spillage, are truly equivalent to those of open surgery remains ongoing.

Additionally, it has been suggested that carbon dioxide (CO_2_) pneumoperitoneum during MIS can stimulate and proliferate tumor cells that spill into the peritoneal cavity. A retrospective analysis demonstrated that total laparoscopic/robotic intracorporeal colpotomy under CO_2_ pneumoperitoneum may carry a risk of a positive vaginal cuff margin, as well as intraperitoneal tumor spreads during MIS (23). Gasless laparoscopy, which was initially developed to overcome clinical and financial challenges associated with pneumoperitoneum and general anesthesia, has been successfully applied in various gynecological and gastrointestinal surgeries (24–26). Many trials have demonstrated the safety and efficiency of gasless laparoscopy (27, 28). However, its potential application in the treatment of cervical cancer and its effect on prognosis warrant further investigation.

In the current study, we aim to conduct a multicenter RCT to compare the oncologic outcomes of early-stage cervical cancer patients (stage IA1 with LVSI, IA2, IB1, IB2) who undergo conventional laparoscopic, gasless laparoscopic or abdominal radical hysterectomy with modifications of technique such as a protective colpotomy and elimination of uterine manipulator usage. Additionally, we will compare the quality of life (QoL), adverse events and surgery-related complications among the different surgical approaches. Furthermore, we will investigate the risk factors affecting the prognosis of cervical cancer in this study. We hope to provide valuable insights into the most effective and safe surgical approach for early-stage cervical cancer and contribute to ongoing efforts to improve patient outcomes and enhance the overall management of the disease.

## Methods

2

### Study design

2.1

This prospective, multicenter, open, parallel, randomized controlled study was mainly focused on investigating the prognosis of early-stage cervical cancer patients who underwent surgical treatments with different approaches. Participants are randomly assigned to receive conventional LRH, gasless LRH or ARH (**Figure 1**). The trial will be conducted in the leading center, Obstetrics and Gynecology Hospital of Fudan University, and the other 3 participating centers in China: Shanghai Sixth People’s Hospital, West China Second University Hospital of Sichuan University and Ruijin Hospital Affiliated to Shanghai Jiaotong University School of Medicine. All four hospitals are Class A tertiary hospitals in China equipped with advanced medical technologies, multidisciplinary health care teams, and robust research capabilities, enabling them to offer comprehensive services related to cervical cancer. The study is registered at http://www.chictr.org.cn/(ChiCTR2000035515, Registered 13 August 2020). Recruitment of participants started in November 2020 and the last participant is expected to reach the primary endpoint (2-year follow-up) in November 2025.

**Figure 1 f1:**
[figure not shown]
Trial scheme. CC, cervical cancer; FIGO, International Federation of Gynecology and Obstetrics; RH, radical hysterectomy; NCCN, National Comprehensive Cancer Network; DFS, disease-free survival; OS, overall survival; QoL, quality of life.

### Participants

2.2

#### Inclusion criteria

2.2.1

Participants meeting all of the following criteria will be considered for enrollment: (1) clinical diagnosis of early stage of cervical cancer (stage IA1 with LVSI, IA2, IB1, IB2, IIA1, 2018 FIGO); (2) histologically confirmed squamous carcinoma, adenocarcinoma or squamous adenocarcinoma of the cervix; (3) age ≥18 years and ≤ 70 years; (4) no history of other malignancies; (5) not pregnant; (6) physical strength classification-Karnofsky score ≥ 60; (7) voluntary agreement to participate in the study, sign the informed consent form, and demonstrate good compliance with follow-up. The tumor stage will be confirmed after independent examination by two senior gynecologic oncologists based on the pathology report and pelvic MRI/CT results. The diagnosis of IA1 with LVSI and IA2 will require the pathology report from the loop electrosurgical excision procedure (LEEP) or conization.

#### Exclusion criteria

2.2.2

Participants meeting any of the following criteria will be excluded (1): contraindicated for various surgical procedures (2); have received pelvic/abdominal radiotherapy irradiation or neoadjuvant chemotherapy for cervical cancer (3); recurrent cervical cancer (4); CT, MRI or PET-CT suggesting suspicious metastasis of lymph nodes or distant metastasis.

### Endpoints

2.3

The primary endpoint is 2-year disease-free survival (DFS). The secondary endpoints include the 2-year overall survival (OS), 5-year DFS/OS, operation time, intraoperative blood loss, surgery-related complications, and quality of life (QoL). DFS and OS will be defined as the interval from the time of surgery to the time of recurrence or death for any reason, respectively. Recurrence will be diagnosed based on radiographic evidence using the Response Evaluation Criteria in Solid Tumors (RECIST) criteria. The EORTC-QLQ-C30 V3.0 questionnaire will be applied to assess the quality of life (QoL).

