### Sample size

3.1

The primary objective of this study was to compare oncologic outcomes among patients undergoing gasless LRH, ARH, and conventional LRH, focusing on 2-year disease-free survival (DFS) as the primary endpoint. Based on previous research results, the estimated 2-year DFS rates for patients undergoing gasless LRH, ARH, and LRH were 97%, 98%, and 96%, respectively. For the study, the noninferiority margin was set at 9%, and there will be a follow-up period of 2 years.

Considering the relative complexity of performing gasless LRH in participant centers compared to leading centers, the sample ratio was set at 2:1:1 (laparoscopy vs. laparotomy vs. gasless laparoscopy group) for statistical analysis, using a one-sided test with a significance level (α) of 0.025. Additionally, a 10% dropout rate, including those lost to follow-up, was assumed for the study. Based on these considerations, the study is estimated to have a statistical power of 97% to detect any survival differences (one-sided test, α=0.025).

In summary, considering the maximum sample size, both the laparotomy group and the gasless laparoscopy group will each require 126 patients, while the laparoscopy group will require 248 patients, resulting in a total of 500 patients needed for the study.

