#### Analysis of primary endpoints

3.3.1

Primary endpoints will be analyzed according to the intention-to-treat principle. Missing data will be censored at the last known date of patient survival. Sensitivity analysis will be performed based on the per-protocol (PP) principle. The study is intended to assess the noninferiority of the 2-year disease-free survival (DFS) rate in the LRH group compared to the ARH and gasless LRH groups, with a noninferiority limit set at 9%.

The DFS rate will be estimated using Kaplan-Meier curves, while the hazard ratio (HR) and one-sided 97.5% confidence interval (CI) will be calculated using a Cox proportional hazards regression model, confirming the proportional hazard assumption. One-sided 97.5% CIs will be reported for DFS differences and HRs, whereas other CIs will be two-sided 95% CIs unless otherwise specified.

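### As worded, the primary DFS endpoint ends only at radiographic recurrence, so a death without documented recurrence is not a DFS event

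*Protocol article*

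**What the plan says.** Section 2.3 (Endpoints) names 2-year DFS as primary and defines DFS and OS in one sentence, as "the interval from the time of surgery to the time of recurrence or death for any reason, respectively". It then says how recurrence is established: "Recurrence will be diagnosed based on radiographic evidence using the Response Evaluation Criteria in Solid Tumors (RECIST) criteria".

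Section 3.1 (Sample size) plans on these values: "the estimated 2-year DFS rates for patients undergoing gasless LRH, ARH, and LRH were 97%, 98%, and 96%, respectively". It does not say which events those rates count. The test settings are "the noninferiority margin was set at 9%, and there will be a follow-up period of 2 years" and "using a one-sided test with a significance level (α) of 0.025".

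Section 3.3.1 tests the 2-year DFS rate of LRH against ARH and gasless LRH, using Kaplan-Meier estimates and a Cox model. Its only censoring rule is "Missing data will be censored at the last known date of patient survival".

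The Abstract and the closing paragraph of the Discussion list recurrence rates among the secondary endpoints. Section 2.3 does not list them.

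**The concern.** DFS ordinarily ends at the first of recurrence or death. Here two endpoints and two events are joined by *respectively*, which assigns recurrence to DFS and death to OS. An analyst following the sentence would produce time to recurrence. A patient who died perioperatively, from adjuvant treatment, or from a relapse never confirmed on imaging would leave the DFS risk set without having failed.

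This matters for two reasons. Such deaths are outcomes that a surgical approach, or the treatment that follows it, can cause, and the primary comparison would not see them. And so few DFS events are planned that a handful of uncounted deaths is a visible share of the total.

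**Working it through.** **1. The wording.** There are two ways to read the sentence.

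- *Paired:* DFS runs from surgery to recurrence, and OS from surgery to death. Every word has a function.
- *Composite:* DFS runs to recurrence or death. Then *respectively* has no function, and OS either shares the composite event or has no event of its own.

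Only the paired reading fits the sentence, and no other section supplies a different DFS definition.

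**2. The plan's own power figure.** Inputs from section 3.1: 2-year DFS 98% (ARH), 97% (gasless LRH), 96% (LRH); margin 9 points; one-sided α 0.025; 126, 126 and 248 patients; 10% dropout, leaving 113.4, 113.4 and 223.2.

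SE = √[p₁(1−p₁)/n₁ + p₂(1−p₂)/n₂], and power = Φ[(0.09 − (p₁−p₂))/SE − 1.96].

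For LRH against ARH, SE = √[0.98×0.02/113.4 + 0.96×0.04/223.2] = 0.0186, and power = Φ(0.07/0.0186 − 1.96) = 96.5%. The same formula gives 97.2% for LRH against gasless LRH and 97.1% for gasless LRH against ARH. The stated 97% is reproduced, so the sample size is not in question.

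**3. Planned events among all 500 patients.**

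- ARH: 126 × 0.02 = 2.5
- Gasless LRH: 126 × 0.03 = 3.8
- LRH: 248 × 0.04 = 9.9
- Total: about 16.2

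**4. Deaths that would not count.** The article gives no rate of death without recurrence, so a range is assumed: 0.2% to 1.0% by 2 years. That is 500 × 0.002 = 1 to 500 × 0.01 = 5 deaths, equal to 6% to 31% of 16.2. At the top of the range, by arm: 1.3 ARH, 1.3 gasless LRH and 2.5 LRH.

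**5. Effect on the LRH-ARH comparison.** Two assumptions apply: the planning rates are recurrence-only, and 1% of patients die without recurrence in the arms named. Figures are after dropout.

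| Case | ARH | LRH | Difference | 1.96 × SE | Power |
|---|---|---|---|---|---|
| Deaths not counted | 98% | 96% | 2 points | 3.6 points | 96.5% |
| Counted, equal in both arms | 97% | 95% | 2 points | 4.2 points | 89.8% |
| Counted, LRH only | 98% | 95% | 3 points | 3.8 points | 86.3% |
| Counted, ARH only | 97% | 96% | 1 point | 4.1 points | 97.2% |

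With equal deaths the difference does not move, and only the interval widens. With unequal deaths, leaving them out flatters LRH if LRH has more and penalises it if ARH has more.

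Over a wider range of assumed rates (0.5%, 1%, 2%), power with the deaths counted is 93.4%, 89.8% and 82.1% if they are equal in every arm, and 92.5%, 86.3% and 67.9% if they fall only in LRH. If the planning rates already include deaths, planned power stays at 96.5%.

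**The case against.** The strongest reply is that this is a slip for ordinary DFS. Recurrence rates appear as a separate secondary endpoint in the Abstract and Discussion and would largely duplicate a recurrence-only DFS. The article also never argues for leaving deaths out. This stands as evidence of intent, but it does not correct the sentence, which is the only definition shown.

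A reader might infer that the definition favours noninferiority. The documents do not support that as a general statement. The margin applies to a difference in rates, and similar death rates in all arms leave it essentially unchanged. Nothing in the article indicates which arm, if any, would have more such deaths. What remains in every case is a narrower interval, because fewer events are counted.

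A reader might also take the section 3.3.1 censoring rule as confirmation that deaths are censored. It is not: that rule covers missing data, and an observed death is not missing. The problem comes from section 2.3 alone.

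It is also fair to say that the effect is small against the margin. Even 1% of deaths, all in LRH, moves the difference from 2 to 3 points against 9. The percentages of the event count look large because the planned event count is so low.

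**Conclusion.** The definition is wrong as written: followed literally, it makes the primary endpoint time to radiographic recurrence. That conclusion rests on the text alone. It does not show that the investigators mean to discard deaths.

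The size depends on an assumed rate. At 0.2% to 1.0%, 1 to 5 deaths go uncounted beside about 16 planned events, with at most about 1 in ARH and 2 to 3 in LRH. Each arm's DFS is overstated by up to the assumed rate, and the interval is somewhat too narrow. Bias in the difference requires an imbalance and can go either way. The power losses above apply only if the planning rates exclude deaths, which section 3.1 leaves open.

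**What to change.** Replace the sentence in section 2.3 with: *DFS is the time from surgery to the first of recurrence or death from any cause; OS is the time from surgery to death from any cause.* This keeps surgery as the time origin; the defect lies in the event, and correcting it does not require a new origin.

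Keep recurrence as its own secondary endpoint and list it in section 2.3, so that it matches the Abstract and Discussion. In section 3.1, state which events the 96% to 98% rates count and confirm that they use the same definition. If they are recurrence-only, restate the power.

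The cost is a short documented amendment. Recruitment began in November 2020 and assignment is open, so the amendment should record its date and reason. Deaths are already collected for OS, so no new data are needed. The event rate may be slightly higher than for recurrence alone.

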### Randomization

2.4

Randomization will be conducted using an online computer algorithm to allocate the radical hysterectomy (RH) approach at a ratio of 2:1:1 (laparoscopy vs. laparotomy vs. gasless laparoscopy group). The computer algorithm will generate a unique code for each participant and collect basic information in addition to group assignment. Patients and study surgeons will be aware of the treatment assignment.

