Standardized postoperative follow-up will be strictly conducted based on the NCCN guideline, with visits scheduled every 3 months for 2 years, every 6 months for the following 3 years, and annually thereafter (**Table S1**). Routine follow-up items will include physical examinations, HPV tests, LCT, ultrasound, enhanced pelvic MRI, PET-CT, and colposcopy when deemed necessary. Moreover, detailed information on complications arising from both surgeries and adjuvant therapy will also be collected during the follow-up period.

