In addition, there is an increasing focus on the safety of minimally invasive approaches in “low-risk” early-stage cervical cancer. The results of the LACC trial were not powered to evaluate the difference in oncologic outcomes of LRH and ARH for patients with “low-risk” cervical cancer. He et al. reported that 5-year OS (96.9% vs. 97.3%, p=0.44) and 5-year DFS (94.5% vs. 95.0%, p=0.22) were similar between LRH and ARH for patients with tumors <2 cm in a multicenter retrospective cohort study in 37 hospitals in China (34). Similar findings were obtained in Chen et al.’s study, which focused on “low-risk” cervical cancer patients with a tumor size<2 cm, no LVSI, superficial stromal invasion, and no lymph node involvement on imaging (35). However, a multi-institutional retrospective review revealed that MIS was associated with higher recurrence, even in patients with a tumor size ≤2 cm (36). Considering that the relatively short-term follow-up might influence the interpretation of the results in this “low-risk” group, a recently published propensity-score based analysis revealed that for low-risk patients, LRH does not result in worse 10-year outcomes than the open approach (37). In this study, we will also try to explore the appropriate approach for “low-risk” early-stage cervical cancer in the subgroup analysis. Considering the distinct biological behavior and prognosis between cervical adenocarcinoma and squamous cell carcinoma (38), we also investigated risk factors including histology, tumor size, FIGO stage, and other pathological characteristics, for the decrease in OS and PFS rate of patients with different surgical approaches. Furthermore, it has been reported that the recurrence pattern differs among cervical cancer patients undergoing LRH or ARH, and the risk factors for recurrence varies in different studies (15, 39–41). In this study, we will also investigate the recurrence risk factors and patterns associated with different surgical approaches.

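### Recurrence has only a stated radiographic route, so a pathologically proven vault recurrence without imaging evidence is not a DFS event, or is dated late

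*Protocol article*

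**What the plan says.** Section 2.3 (Endpoints) of the protocol article makes 2-year DFS the primary endpoint. It gives one sentence on how recurrence is established: "Recurrence will be diagnosed based on radiographic evidence using the Response Evaluation Criteria in Solid Tumors (RECIST) criteria". The same section defines DFS and OS together as "the interval from the time of surgery to the time of recurrence or death for any reason, respectively".

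The follow-up paragraph of section 2.6 (Treatments) sets visits every 3 months for the first 2 years. It lists the tests: "Routine follow-up items will include physical examinations, HPV tests, LCT, ultrasound, enhanced pelvic MRI, PET-CT, and colposcopy when deemed necessary". Several of these are not imaging. Nothing says whether a positive finding from one of them, confirmed by biopsy or cytology, is a DFS event, or what date it would carry.

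Two other places bear on the site of recurrence. The Introduction cites a retrospective analysis in which laparoscopic or robotic colpotomy under CO2 "may carry a risk of a positive vaginal cuff margin, as well as intraperitoneal tumor spreads during MIS". The Discussion adds that "it has been reported that the recurrence pattern differs among cervical cancer patients undergoing LRH or ARH". Section 2.4 (Randomization) states that the trial is open: "Patients and study surgeons will be aware of the treatment assignment".

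**The concern.** The tests scheduled in section 2.6 can lead to tissue or cytological proof of disease at the vaginal vault before imaging shows anything. Under section 2.3 such a patient has not recurred. Two things can then happen.

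- Imaging later becomes positive, and the event is dated at that point. If that falls after month 24, a true 2-year event leaves the 2-year rate.
- Imaging never meets the criterion, and the recurrence is not counted. A later death might still bring the patient in, but the word "respectively" in the definition of DFS and OS leaves open whether death counts towards DFS.

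The test is one of noninferiority on a difference in 2-year DFS. Losing true events pulls both observed rates towards 100% and compresses the difference, so incomplete capture makes noninferiority easier to declare. The expected number of events is small, so one or two uncounted cases matter. The spillage hypotheses behind the trial concern colpotomy, so the vault is a site where the endpoint rule ought to be clear.

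**Working it through.** **Inputs (section 3.1, Sample size).** Assumed 2-year DFS: ARH 98%, gasless LRH 97%, LRH 96%. Margin M = 9 points. One-sided α = 0.025. Dropout 10%. Enrolled: 126 ARH, 126 gasless, 248 LRH. Stated power: 97%. The documents give no share of recurrences proven without imaging, so 10-30% is an assumed range.

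**1. The plan's own figure.** With C the comparator and T the tested arm:

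SE = √[pC(1−pC)/nC + pT(1−pT)/nT], power = Φ[(M − (pC − pT))/SE − 1.96].

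- Evaluable after dropout: 126 × 0.9 = 113.4 and 248 × 0.9 = 223.2.
- ARH vs LRH: SE = √(0.98×0.02/113.4 + 0.96×0.04/223.2) = 0.01857. Then (0.09 − 0.02)/0.01857 = 3.77, and power = Φ(1.81) = 96.5%.
- ARH vs gasless: 97.1%. Gasless vs LRH: 97.2%.
- Solving ARH vs gasless for 97% power gives 113 per arm, and 113/0.9 = 126.

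The stated design is reproduced, so the formula is suitable for what follows.

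**2. Expected events by 2 years, after dropout.** LRH 223.2 × 0.04 = 8.9. ARH 113.4 × 0.02 = 2.3. Gasless 113.4 × 0.03 = 3.4.

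**3. Shift in the ARH-LRH difference if a share f of recurrences is lost completely.** Event rates in points:

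- Lost equally in both arms: 4(1−f) − 2(1−f) = 2(1−f). The difference shrinks by 2f, which is 0.2 points at f = 10% and 0.6 at 30%.
- Lost in LRH only: 4(1−f) − 2. The difference shrinks by 4f, which is 0.4 to 1.2 points.
- In numbers of events: 0.9-2.7 of 8.9 in LRH and 0.2-0.7 of 2.3 in ARH.

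**4. Shift if the cases are only delayed.** Assume imaging confirms each case one visit (3 months) later and events are uniform over 24 months. Then 3/24 = 1/8 of the affected cases cross month 24.

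- Equal in both arms: 2f/8 = 0.025 to 0.075 points.
- LRH only: 4f/8 = 0.05 to 0.15 points, or about 0.1-0.3 LRH events.

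**5. Effect on a false claim of noninferiority.** Put the true rates at the margin: ARH 98%, LRH 89%. With complete capture, the chance of declaring LRH noninferior is 2.5%. With a share f lost, replace the event rates 2% and 11% by their observed values. Example, f = 20% in LRH only: the LRH event rate is 8.8%, the difference 6.8 points, SE 0.0231, and Φ(0.022/0.0231 − 1.96) = 15.7%.

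| Share affected | Lost, both arms | Lost, LRH only | One-visit delay, both arms | One-visit delay, LRH only |
|---|---|---|---|---|
| 10% | 5.7% | 6.7% | 2.8% | 2.8% |
| 20% | 12.4% | 15.7% | 3.1% | 3.2% |
| 30% | about 25% | 31.9% | 3.4% | 3.7% |

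Loss in ARH only would act the other way: 2.1% at a 10% share and 1.3% at 30%.

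**6. At the planning rates.** Losing 20% of LRH events only moves the observed difference from 2.0 to 1.2 points and power from 96.5% to 99.3%. This makes noninferiority easier to declare; it does not reverse a conclusion.

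**The case against.** **The text does not say that imaging is the sole route.** This is true, and a reader might go further and infer that histology is expressly ruled out. The article does not say that. It gives one route and no other, so exclusion is what follows from applying the sentence as it stands. Nor is this just detail left to a fuller protocol: the article does state the diagnostic rule, and the rule as stated omits pathology.

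**RECIST needs measurable disease, and resected patients have none.** This stronger reading is tempting, but section 2.3 does not mention measurability. A new lesion on imaging can be radiographic evidence, so the point should rest on the absence of radiographic evidence and not on lesion size.

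**Late is not lost.** This stands and limits the size considerably. Visits are 3-monthly, and MRI and PET-CT are among the listed tests. Many cases would be confirmed later and still fall within 24 months. The article does not state how often imaging is done, so delays longer than one visit are possible. Complete loss is the extreme case.

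**No bias by approach is shown.** This also stands. The Introduction's citation concerns positive cuff margins and intraperitoneal spread, not vault recurrence. The Discussion says patterns differ, not that vault-only disease is commoner after LRH. Section 2.6 requires vaginal closure and bans manipulators in every arm.

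**A radiographic standard protects an open trial from selective searching.** This has some force, because colposcopy "when deemed necessary" could be prompted by knowing the assignment. But histological or cytological proof is itself objective, and a radiographic-only sensitivity analysis retains the protection.

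**Conclusion.** The point holds in a limited form. The stated rule misclassifies or misdates a pathologically proven recurrence that lacks radiographic evidence, in the primary endpoint.

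The documents do not allow its size to be fixed. On the assumption that 10-30% of recurrences are affected, complete and equal loss shrinks the ARH-LRH difference by 0.2-0.6 points, and loss in LRH only by 0.4-1.2 points. A one-visit delay shrinks it by 0.15 points at most. These shifts should be read against the 9-point margin as well as the planned 2-point difference.

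Under-capture tends to favour noninferiority even when balanced, provided LRH truly has the higher event rate. The point therefore does not depend on imbalance. A reader might infer that the rule flatters LRH in particular. That is possible, but the documents do not show it. The larger error rates in the table require both complete loss and a true difference at the margin, so they bound the problem and do not forecast it. The change is worth making because it is cheap and removes an avoidable bias.

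**What to change.** Amend section 2.3 so that recurrence is the earlier of:

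- (a) histological or cytological confirmation of recurrent cervical cancer; or
- (b) radiographic evidence of recurrence by the existing criterion, whether or not a biopsy was feasible.

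Date the event at the first of the two. Apply the rule identically in all three arms and to recurrences already recorded. Keep DFS on the radiographic-only definition as a sensitivity analysis. Route (b) must not be made conditional on biopsy being impossible, because imaged recurrences that were never biopsied would then drop out.

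The cost is a short amendment, one eCRF field for the basis of diagnosis, and a review of recurrences recorded since recruitment began in November 2020. Event rates would be slightly higher. The sample size need not change, and the tests are already part of follow-up.
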